## Abstract

**Trial registration::**

The study was registered the jRCTs072200018. URL https://jrct.niph.go.jp/latest-detail/jRCTs072200018

## Introduction

1

Respiratory failure is the most common postoperative pulmonary complication. In head and neck surgery where the oropharyngeal area is the operative field, postoperative respiratory depression and upper airway obstruction are particularly common. Routine oxygen administration aims to prevent this postoperative early hypoxemia. Furthermore, it may be recommended to administer oxygen with a certain allowance, such as until the next morning if the operation is highly invasive or if the operation end-time is during the night-shift with reduced staff numbers. Therefore, there is increased likelihood of administering greater levels of oxygen in these patients than required. The routine administration of oxygen does not address the problem of hypoventilation, may lead to CO_2_ retention and may delay the discovery of worsening respiratory function.^[1]^

Nasal high flow (NHF) is drawing attention as a respiratory support therapy. NHF generates high flows (up to 60 L/min) of heated and humidified gas delivered via nasal cannula. NHF provides respiratory support by generating positive airway pressure, clearance of dead space, reduction of work of breathing and improved mucociliary clearance.^[2–5]^ NHF can be delivered as room air only or with supplemental oxygen, depending on the context.

In a recent study, NHF with room air and no supplemental oxygen was effective as a respiratory support method under spontaneous breathing during moderate propofol sedation.^[6]^ It has been reported that transcutaneous CO_2_ partial pressure and SpO_2_ can be maintained in the normal range by reducing respiratory effort. Therefore, it is possible that NHF without the combined use of oxygen can be an effective therapy for patients during the postoperative acute phase. If NHF with room air and no supplemental oxygen can prevent postoperative early hypoxemia, the authors believe that safer respiratory management will be possible in general wards.

This research aims to determine whether postoperative hypoxemia and hypercapnia can be prevented by NHF. The authors’ hypothesis is that an application of NHF without oxygen supplement may prevent hypoxemia and hypercapnia after surgery under general anesthesia. Furthermore, the study is designed to investigate whether spontaneous breathing alone with no respiratory support is safe, therefore testing the efficacy and necessity of conventional oxygen administration. As there have been no previous studies related to this purpose, there is no basis for calculating the sample size. Therefore, this research will be conducted as an exploratory exercise, and the main of full-scale clinical study will be carried out as the next stage based on the results. Through this study and the verification studies planned after that, if hypoxemia and hypercapnia can be prevented by using NHF in the postoperative acute phase, safer and more comfortable acute respiratory management will be possible.

## Methods/design

2

### Study design

2.1

The present study was designed in accordance with the Standard Protocol Items: Recommendations for Interventional Trials and Consolidated Standard of Reporting Trials 2010 guidelines.^[7,8]^ This will be a randomized controlled trial (RCT) in patients scheduled for oral-maxillofacial surgery under general anesthesia.

The Clinical Research Review Board at Nagasaki University approved the study. The trial will be conducted at Nagasaki University Hospital in Japan and is registered on the RCTs. The study will be conducted in accordance with the principles of the Declaration of Helsinki and the established best clinical practices of Japan.

This is an exploratory study and therefore, the sample size is set based on the feasibility in the hospital. For efficacy purposes, the time-weighted average value of transcutaneous CO_2_ partial pressure (tcpCO_2_), transcutaneous O_2_ partial pressure (tcpO_2_), SpO_2_, and respiratory rate during the observation period will be evaluated.

### Participant recruitment

2.2

The study will recruit adult patients undergoing planned oral surgery under general anesthesia at Nagasaki University Hospital. It is a randomized parallel group comparative study with 3 groups. After obtaining informed consent, the target patients who meet the registration requirements will be randomly assigned to one of the 3 groups (ratio 1:1:1). The groups are as follows: Experimental group - NHF with room air only and no supplemental oxygen; Control group 1 - no respiratory support; Control group 2 - face mask oxygen administration (oxygen 5 L/min use) (Fig. 1).

**Figure 1 F1:**
[figure not shown]
After obtaining informed consent, 48 subjects who meet the registration requirements will be randomly assigned to either of the 3 groups. The experimental group will be: Experimental group - NHF with room air only and no supplemental oxygen; Control group 1 - no respiratory support; Control group 2 - face mask oxygen administration (oxygen 5 L/min use). NHF = nasal high flow.

### Inclusion criteria

2.3

Target patients who meet all of the following criteria:

1.Patients scheduled for oral-maxillofacial surgery under general anesthesia2.Patients who have been given sufficient information about the study and have provided their full understanding and consent to the patient's free will3.At the time of obtaining consent, an adult patient between 20 and 85 years old

### Exclusion criteria

2.4

Patients who meet at least one of the following are to be excluded:

1.Patients who have already been receiving continuous oxygen (home oxygen therapy)2.Patients who cannot breathe through their nose3.Patients who cannot reduce or discontinue antithrombotic drugs after surgery4.Patients with a history of pneumothorax5.Patients who the investigator judged to be inappropriate for the study6.Severe acute respiratory syndrome coronavirus polymerase chain reaction test positive patients

#### Sample size

2.4.1

The study is exploratory and aims to collect information for conducting verification research. Therefore, the sample size is set based on the feasibility. There are about 240 patients who undergo oral surgery within 5 hours under general anesthesia at Nagasaki University Hospital in 1 year. If we estimate that about 60% of the cases in the 4-month (80 cases) are available for obtaining consent, target sample size is 48. The 48 cases of oral surgery will be divided into the 3 groups: NHF with room air, 16 cases; face mask oxygen administration, 16 cases; and no respiratory support, 16 cases.

### Study protocol

2.5

The study protocol will begin at the time that the patient is returned to the general ward and will finish 3 hours later. Patients assigned to the NHF group will be placed on NHF therapy with a starting flow rate of 40 L/min at the time of returning to the general ward. As with normal respiratory management in the general ward, if SpO_2_ shows a value of 90% or less due to a factor other than body movement during NHF use and the monitor alarm is activated, then supplemental oxygen may be applied until SpO_2_ returns to above 90%. Patients may request to remove the NHF cannulas, at which time they may switch to oxygen administration by face mask.

Patients assigned to the face mask oxygen administration group will be started on 5 L/min supplemental oxygen (FiO_2_ around 0.4) via face mask starting at the return to the general ward until 3 hours later. The level of supplemental oxygen will be adjusted to maintain SpO_2_ above 90%.

In the group that will not receive respiratory support upon arrival in the ward, each patient will be monitored and if the SpO_2_ remains at ≤90% then the patient will be placed on face mask oxygen administration, and administration of oxygen will start at 5 L/min until SpO_2_ returns to the normal value above 90%.

After the operation, the vital signs of the patient will be evaluated, including blood pressure, electrocardiogram, and SpO_2_, which are the usual measurements in general wards. Separate to these assessments, the partial pressure of tcpCO_2_, partial pressure of tcpO_2_ and respiratory rate will be continuously monitored. To continuously measure the breathing parameters, respiratory inductance plethysmography will be used (QDC-Pro, made by CareFusion). The chest and abdominal movements is traced, and analog data will be output externally and recorded in PowerLab. In addition, the tidal volume, respiratory rate, and minute ventilation are calculated from the measured data.

### Adverse events

2.6

During the study, it is possible that the NHF interface or oxygen face mask may cause discomfort. Moreover, an electrode for transcutaneous measurement of oxygen and CO_2_ concentration will be attached to the anterior chest. For participants with sensitive skin, this might cause temporary redness. If and when these adverse events occur, care will be taken to prevent undue harm to the research subjects.

### Outcome

2.7

The primary endpoint is: time-weighted average of tcpO_2_ over the 180 minutes. The secondary endpoints are: time-weighted average of tcpCO_2_, time-weighted average of SpO_2_, time-weighted average of respiratory rate, incidence rate of marked hypercapnia in which tcpCO_2_ is maintained at 60 mm Hg or higher (equivalent to PaCO_2_ >55 mm Hg for 5 minutes or longer), incidence rate of moderate hypercapnia with tcpCO_2_ of 50 mm Hg or more (equivalent to PaCO_2_ >45 mm Hg), percentage of SpO_2_ that fell below 90% and required oxygen administration. The weighted average partial pressure will be calculated, which is the weighted average value for 3 hours (180 minutes), considering the time width between the measurement points.

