## Discussion

3

Patients undergoing surgery under general anesthesia are often given oxygen through a nasal cannula or face mask to prevent hypoxemia in the general ward during the postoperative acute period. As a result, respiratory management can be performed so that the value of percutaneous arterial oxygen saturation is maintained >90%. However, postoperative acute respiratory management should be to maintain normal respiratory function and gas exchange with normal range of CO_2_, and not to merely maintain apparent SpO_2_. Furthermore, it is necessary to be careful when administering a high concentration of oxygen to patients, and if the oxygen level is raised, there is a risk of developing secondary respiratory complications.

In a recent study, NHF with no supplemental oxygen proved to be effective as a respiratory support method under spontaneous breathing during moderate propofol sedation. It has been reported that the partial pressure of transcutaneous CO_2_ and SpO_2_ can be maintained in the normal range by reducing the breathing effort.^[6]^ Therefore, it is possible that NHF without the combined use of oxygen can be effective for patients who are in the state of somnolence or sedation due to the effects of anesthetics during the postoperative acute phase.

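### The aim is to prevent hypoxemia, but the oxygenation endpoints are 180-minute averages and the only hypoxemia event endpoint counts episodes only if oxygen was required

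*Protocol article*

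**What the plan says.** All references are to the protocol article.

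- **Aim (section 1, Introduction).** "This research aims to determine whether postoperative hypoxemia and hypercapnia can be prevented by NHF". The hypothesis is that "an application of NHF without oxygen supplement may prevent hypoxemia and hypercapnia after surgery under general anesthesia". The Introduction also says of current practice: "Routine oxygen administration aims to prevent this postoperative early hypoxemia". Section 3 (Discussion) adds that the no-support arm is there to see whether spontaneous breathing alone avoids hypoxemia.
- **Primary endpoint (section 2.7, Outcome).** "The primary endpoint is: time-weighted average of tcpO_2_ over the 180 minutes". It is formed as "the weighted average value for 3 hours (180 minutes), considering the time width between the measurement points".
- **Secondary endpoints (section 2.7).** SpO2 is also summarised as a time-weighted average. Hypercapnia has two threshold endpoints, at tcpCO2 of 60 and 50 mm Hg. Hypoxemia has one event endpoint, which needs both SpO2 below 90% and a requirement for oxygen.
- **Window (section 2.5, Study protocol).** "The study protocol will begin at the time that the patient is returned to the general ward and will finish 3 hours later". Rescue oxygen is possible inside this window.
- **Analysis (section 2.10).** There is no hypothesis testing. Point estimates with 95% confidence intervals are reported and will be used to size the main study. The Discussion says that valid measures of efficacy are not yet known.

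**The concern.** Whether hypoxemia was prevented is a question about events. A mean over three hours lets high readings offset low ones, so a short desaturation hardly moves it. If the desaturation is treated with oxygen, the treatment itself enters the mean and pushes it up.

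The secondary event endpoint would normally cover this gap, but it is tied to a treatment decision. A patient whose SpO2 falls and recovers without oxygen is counted by no listed efficacy endpoint. Whether oxygen is given depends on a rule that is not the same in the three arms.

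At stake is what the trial hands to the next one. It is meant to supply estimates for a main study and, by its own account, does not yet know which efficacy measure is valid. As listed, the endpoints provide no measure of hypoxemia that has the same meaning in every arm.

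**Working it through.** **The plan's own figure.** Section 2.4.1 gives about 240 cases a year, 4 months and 60% consent: 240 × 4/12 = 80; 80 × 0.60 = 48; 48/3 = 16 per arm. The stated sample size reproduces. No alpha, power, effect size or SD is given, so no power calculation applies.

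**1. Is the event endpoint the same quantity in each arm?** Section 2.5, set side by side:

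- NHF: oxygen is permitted, not mandated, when SpO2 is 90% or less for a reason other than movement and the alarm is activated.
- No support: mask oxygen is started if SpO2 stays at 90% or less.
- Mask: oxygen runs from arrival on the ward and its level is adjusted to keep SpO2 above 90%.

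The same fall in SpO2 can therefore count in one arm and not in another. In the mask arm, requiring oxygen has no clear meaning. The threshold differs too: the rescue rules use 90% or less, whereas the endpoint uses below 90%.

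**2. How much does a short episode move a 180-minute average?** Shift = depth × minutes / 180. The article gives no depths or durations, so these values are assumed.

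- tcpO2 fall of 20 to 30 mm Hg for 5 minutes: 20 × 5/180 = 0.56 to 30 × 5/180 = 0.83 mm Hg.
- The same fall for 10 minutes: 1.1 to 1.7 mm Hg. For 30 minutes: 3.3 to 5.0 mm Hg.
- SpO2 from 96% to 85% for 5 minutes: 96 − 11 × 5/180 = 95.69%.

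**3. Can rescue oxygen reverse the signal?** Assume a baseline tcpO2 of 75 mm Hg, 5 minutes at 50, then m minutes on oxygen at 135, then a return to 75. Average = [75 × (175 − m) + 50 × 5 + 135 × m] / 180.

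- m = 15: (12,000 + 250 + 2,025)/180 = 79.3
- m = 30: (10,875 + 250 + 4,050)/180 = 84.3
- m = 60: (8,625 + 250 + 8,100)/180 = 94.3

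All exceed the 75 of a patient who never desaturated. The dip removes 25 × 5 = 125 mm Hg·minutes, and oxygen adds 60 per minute, so the break-even is 125/60 = 2.1 minutes. If oxygen raised tcpO2 by only 20 mm Hg, it would be 125/20 = 6.25 minutes.

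**4. Precision at 16 per arm.** The 95% confidence interval for a difference in means between two arms has half-width t(0.975, 30) × √(2/16) = 0.72 SD. Exact 95% intervals for an event proportion are 0 to 20.6% (0/16), 0.2 to 30.2% (1/16), 1.6 to 38.3% (2/16) and 7.3 to 52.4% (4/16). An event proportion would be imprecise, which is a reason to add one rather than make it primary.

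**The case against.** - **Hypoxemia is not assessed by the primary average alone.** This is correct. Section 2.7 lists an SpO2 event endpoint, and section 2.8 counts abnormal vital signs as adverse events. A reader might infer that one average decides the question; the article does not support that. What remains is that the event endpoint is secondary and tied to oxygen. Section 2.8 gives no SpO2 threshold or duration, so it supplies no comparable estimate.
- **Sustained desaturation would trigger rescue and be counted.** This largely holds in the no-support arm, so the gap there is mainly brief dips. It is wider under the permissive NHF wording, and the endpoint is undefined in effect for the mask arm.
- **A continuous primary endpoint suits a small exploratory study, and descriptive detail belongs in an analysis plan.** The first part stands, so the primary endpoint need not change. On the second, hourly summaries could well sit in a plan that is not shown. The oxygen condition on the event endpoint, however, is fixed in section 2.7 itself.
- **Continuous SpO2 recording is not stated.** This also stands. Section 2.5 names tcpCO2, tcpO2 and respiratory rate as continuously monitored and lists SpO2 among the usual ward measurements. But a time-weighted SpO2 average already needs a timed series of readings, and the added measures can use that series at whatever resolution it has.

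**Conclusion.** The concern holds as a mismatch between aim and endpoints. The averages respond little to short episodes, and the primary one can rise after a desaturation treated with oxygen. The only event measure is conditional on treatment under rules that differ by arm. The section 2.5 and 2.7 comparison rests on the text alone. The sizes in mm Hg and SpO2 rest on assumed values and show direction and order of magnitude only. With no test planned, no power is lost; the cost is a weaker basis for choosing and sizing the main-study endpoint.

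A reader might go further and infer that averaging over three hours dilutes an effect confined to early recovery, so that a main study would come out 9 times too large. The article does not support this. The Introduction speaks of early hypoxemia without defining it in minutes, and the three hours may be the early phase meant. The Discussion refers to "patients who are in the state of somnolence or sedation due to the effects of anesthetics during the postoperative acute phase" but sets no hour limit.

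Even if the effect were confined to the first 60 minutes, 9 would be a ceiling. With equal hourly SDs and correlation ρ between hourly means, the ratio of sample sizes (180-minute against 60-minute mean) is 3 + 6ρ: 6 at ρ = 0.5, and 9 only at ρ = 1. For an effect lasting 120 minutes the ratio is 1.5(1 + 2ρ)/(1 + ρ): 2.0 at ρ = 0.5, and 2.25 only at ρ = 1. Dilution is a possibility to check, not a finding.

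**What to change.** Keep the primary endpoint and N = 48. Add to section 2.7:

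1. The proportion of patients with any SpO2 at or below 90%, and the percentage of the 180 minutes spent there. Take both from the record used for the planned SpO2 average, and define them identically in all three arms whether or not oxygen was given.
2. Rescue oxygen as a separate item by arm, not as a condition of the hypoxemia measure.
3. The time-weighted averages by hour (0–60, 60–120 and 120–180 minutes) as descriptive estimates beside the overall value.

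State that these, together with the overall average, will inform the endpoint and window of the main study. The rescue rules need no change for this purpose, but the 90% boundary in sections 2.5 and 2.7 should be reconciled.

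The cost is wording and a little computation. With no testing there is no multiplicity penalty. There are three drawbacks: the added estimates are imprecise at 16 per arm, their resolution is limited by how often SpO2 is recorded, and time at or below 90% is itself shortened by rescue oxygen. The last is why rescue should be reported alongside.

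### The secondary endpoint that pairs SpO2 below 90% with a need for oxygen does not match the oxygen rules: its cut-off differs from the trigger, the rule varies by arm, and the event is undefined in the mask arm

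*Protocol article*

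**What the plan says.** Section 2.7 (Outcome) of the protocol article names six secondary endpoints. The last is the "percentage of SpO_2_ that fell below 90% and required oxygen administration". It has two parts: a fall in SpO2 and a need for oxygen.

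Section 2.5 (Study protocol) sets out when oxygen is given, arm by arm:

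- **NHF with room air.** The rule applies "if SpO_2_ shows a value of 90% or less due to a factor other than body movement during NHF use", and continues: "the monitor alarm is activated, then supplemental oxygen may be applied until SpO_2_ returns to above 90" per cent. There is a second route to oxygen with no SpO2 condition: "Patients may request to remove the NHF cannulas, at which time they may switch to oxygen administration by face mask".
- **No respiratory support.** The rule is that "if the SpO_2_ remains at ≤90% then the patient will be placed on face mask oxygen administration".
- **Face mask oxygen.** Patients "will be started on 5 L/min supplemental oxygen (FiO_2_ around 0.4) via face mask starting at the return to the general ward". After that, "The level of supplemental oxygen will be adjusted to maintain SpO_2_ above 90" per cent.

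Section 2.10 (Statistical analysis) plans no hypothesis tests. It plans point estimates with 95% confidence intervals for the efficacy endpoints, and says the estimates will be used to size the main study.

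**The concern.** The introduction asks whether NHF without oxygen prevents hypoxaemia, whether breathing without support is safe, and whether routine oxygen is needed. Among the listed endpoints, this is the only one that counts hypoxaemia events. The other oxygenation endpoints are averages over 180 minutes, which can hide short desaturations.

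An event that requires both a desaturation and oxygen depends on how low SpO2 went and on what the staff were told to do about it. If those instructions differ by arm, arms with the same desaturations can show different rates. If one arm is on oxygen throughout, the second half of the definition does not discriminate there. The comparison of no support with mask oxygen, which bears on whether oxygen is needed, then rests on a quantity that one side does not define.

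**Working it through.** **Trial size.** Section 2.4.1 gives about 240 cases a year, a 4-month window and 60% consent: 240 / 12 × 4 = 80; 80 × 0.60 = 48; 48 / 3 = 16 per arm. This agrees with the article. The point challenges no stated number; 16 is used below only as a denominator.

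**Endpoint and oxygen rules side by side.**

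| | Endpoint (2.7) | NHF (2.5) | No support (2.5) | Mask (2.5) |
|---|---|---|---|---|
| SpO2 level | below 90% | 90% or less | 90% or less | kept above 90% |
| Qualifier | none | not due to movement; alarm activated | low reading persists, no duration given | none |
| Oxygen | required | may be given | will be given | already running; level adjusted |
| Other route to oxygen | not addressed | on patient request | none stated | not applicable |

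**Cut-off.** A reading of exactly 90% meets the trigger in both room-air arms but not the endpoint. Oxygen given at 90% may also stop the further fall that would have counted. The article gives no frequency for such episodes.

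**Oxygen part, room-air arms.** Let p be the true proportion of patients who desaturate and f the share of those episodes that lead to oxygen under the arm's rule. The recorded rate is p × f. With the same p in both arms, the spurious difference is p × (f1 − f2). The documents give neither p nor f, so these are assumptions:

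| p | f = 0.5 | f = 0.7 | f = 0.9 | f = 1.0 |
|---|---|---|---|---|
| 20% | 10% | 14% | 18% | 20% |
| 30% | 15% | 21% | 27% | 30% |
| 40% | 20% | 28% | 36% | 40% |

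At p = 30%, f from 0.5 to 1.0 gives 16 × 0.15 = 2.4 to 16 × 0.30 = 4.8 recorded events in 16 patients, with no treatment effect. The largest spurious difference in that row is 30 − 15 = 15 percentage points. It could favour either arm. A permissive rule in NHF lowers f there; a requirement that the low reading persist lowers f in the no-support arm.

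**Oxygen part, mask arm.** Section 2.7 does not say what the need for oxygen means for a patient already receiving it. The possible readings give different results:

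- Only newly started oxygen counts: 0/16 whatever happens, exact 95% interval 0 to 1 − 0.025^(1/16) = 20.6%.
- The oxygen part is met by design: the event becomes any SpO2 below 90%.
- A rise in oxygen after a fall counts: possible, since the level is adjusted, but not stated.
- Everyone on oxygen counts: 16/16, exact 95% interval 0.025^(1/16) = 79.4% to 100%. This ignores the SpO2 half and is the least plausible reading.

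**The case against.** The strongest reply is proportion. This is the last of six secondary endpoints in an exploratory trial with no tests. The primary endpoint, the time-weighted average of tcpO2, does not use it, and the sample size comes from feasibility. That stands and sets the severity. Section 2.10 does pass estimates on to the main study, but it does not name this endpoint as the one that will size it.

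Second, the two room-air arms are closer than they may look. They share the level of 90% or less and the same stopping point. The NHF rule is introduced as normal ward practice, and an alarm may have a delay, so it need not mean a single reading. This also stands: comparability between NHF and no support is weakened, not abolished.

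Third, with 16 per arm the intervals are wide anyway: 4/16 has an exact 95% interval of 7.3% to 52.4%. True, but the interval does not reveal a difference created by the definition, and a larger main study using the same definition would not remove it.

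Fourth, a condensed article may leave persistence times and artefact handling to the full protocol or analysis plan. Agreed; their absence is not the point. The conflict between 2.5 and 2.7 stands in the printed text.

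A reader might infer two stronger things. One is that the mask arm's rate is zero by definition; that is only one of the readings above. The other is that the definition manufactures a benefit for NHF; the wording can push either way, and the documents contain no figures from which to compute a size. Nor does the endpoint lack all meaning in the mask arm, since SpO2 below 90% can still be measured there.

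**Conclusion.** The point holds as a mismatch between sections 2.5 and 2.7. The cut-off differs from the trigger, the oxygen half of the event follows a different rule in each room-air arm, and it is undefined in the mask arm. The text alone establishes these three facts, without any assumption.

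The consequence is that the rates partly describe the oxygen rule of the arm. The range of 15% to 30% recorded for the same true 30% rests on assumed values of p and f, and shows only that the effect could be appreciable; its direction is unknown. This should be fixed, at a level fitting one secondary endpoint. The primary endpoint and the sample size of 48 are untouched.

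**What to change.** Redefine the endpoint in section 2.7 as the percentage of patients who meet one SpO2 criterion. Apply it identically in all three arms, whether or not oxygen was given, to the SpO2 values already recorded for the time-weighted average. Report separately the percentage in whom oxygen was started (NHF and no support, with a switch at the patient's request shown apart) and the percentage in whom oxygen was increased (mask).

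The investigators must reconcile the cut-off in 2.7 with the trigger in 2.5, and the oxygen rules of the arms with one another. This review takes no view on which clinical trigger is right.

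The cost is rewording and a little extra data processing. Two limits remain. The event can be no finer than the recorded SpO2: section 2.5 lists SpO2 with the usual ward measurements and does not say that a continuous trace is stored. And oxygen given under differing rules still affects later SpO2, so a common event definition reduces the dependence on the oxygen rule but does not remove it entirely.
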